**Methods:**

We plan to recruit a cohort of 1,600 patients, male or female, with advanced fibrosis or cirrhosis (i.e., F3 or F4) and MELD ≤ 15, in Vietnam and Saudi Arabia (*n* = 800 each). Individuals with a liver mass ≥ 1 cm in diameter, elevated alpha-fetoprotein (AFP) (≥ 9 ng/mL), and/or elevated GALAD score (≥ -0.63) will be scanned with dynamic contrast-enhanced magnetic resonance imaging (MRI), and a diagnosis of HCC will be made by Liver Imaging Reporting and Data System (LiRADS) assessment (LiRADS-5). Additionally, those who do not exhibit abnormal imaging findings, elevated AFP titer, and/or elevated GALAD score will obtain a dynamic contrast-enhanced MRI annually for five years to assess for HCC. Only MRI nearest to the time of GALAD score measurement, ultrasound and/or AFP evaluation will be included in the diagnostic validation analysis. MRI will be replaced with an abdominal computed tomography scan when MRI results are poor due to patient conditions such as movement etc. Gadolinium-ethoxybenzyl-diethylenetriamine pentaacetic acid-enhanced MRI will not be carried out in study sites in both countries. Bootstrap resampling technique will be used to account for repeated measures to estimate standard errors and confidence intervals. Additionally, we will use the Cox proportional hazards regression model with covariates tailored to the hypothesis under investigation for time-to-HCC data as predicted by time-varying biomarker data.

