### Outcome measures

The primary endpoint is the performance of GALAD score determined in association with HCC detection by LiRADS criteria in a cohort with advanced fibrosis or cirrhosis (e.g., Metavir F3 or higher, with MELD 15 or lower) undergoing prospective surveillance every six months for five years. Performance of GALAD score will be determined by using the GALAD score cut-off value of -0.63 to prospectively survey a cohort of 1,600 patients with advanced fibrosis and early cirrhosis (e.g., Metavir F3 or higher, with MELD 15 or lower) for early detection of HCC by Liver Imaging Reporting and Data System (LiRADS) assessment (LiRADS-5). The GALAD cut-off value was previously determined in case–control studies [11]. For the establishment of the biorepository, the endpoint is the proportion of study participants who agree to consent for bio-specimen when invited.

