**Fig. 2 Fig2:**
[figure not shown]
Study Schema. Patients with chronic liver diseases from hospital database of the participating sites will be screened and invited for enrollment if eligible. Next, we prospectively survey the eligible cohort of patients at risk for HCC (i.e. patients with advanced fibrosis or compensated cirrhosis and irrespective of cirrhosis etiologies), using semi-annual abdominal ultrasound and GALAD Score for five years. During the 5-year follow-up, individuals with a liver mass ≥ 1 cm in diameter and/or elevated GALAD score (≥ -0.63) will be scanned with dynamic contrast-enhanced MR,I and a diagnosis of HCC will be made by LiRADS assessment (LiRADS-5). Additionally, those who do not exhibit abnormal imaging findings and/or elevated GALAD score will obtain a dynamic contrast-enhanced MRI annually for five years to assess for HCC

During the 5-year time frame, we anticipate at least 80 (approximately 16 each year if 1% incidence x five years for both cohorts in Vietnam and Saudi Arabia) or as many as 320 (64 per year if 4% incidence x five years for both cohorts in Vietnam and Saudi Arabia) incident HCC cases given the high HCC incidence rate in Vietnam and Saudi Arabia. With the range of 80 to 320 anticipated HCC cases, we will have 90% to 99% power, respectively, to detect a meaningful difference in the cases vs. control (more on sample size calculation below). We will compare sensitivity for early HCC detection (primary outcome measures), false-positive results, and resultant diagnostic evaluation.

By leveraging the prospective cohort, we will establish a biorepository of longitudinally collected biospecimens from patients with fibrosis/cirrhosis to be used as a reference set for future research. Clinical, laboratory, and imaging data, urine, and plasma biospecimens are from participants for up to five years; data are collected only from participants who maintain the absence of evidence of HCC on imaging and/or biopsy. Biospecimens and associated de-identified clinical data from participants enrolled in this study will be stored in Vietnam for participants from Vietnam and in Saudi Arabia for participants enrolled from Saudi Arabia.

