### GALAD score

This study is considered a prospective observational cohort study. GALAD score, comprising Gender, Age, AFP-L3, AFP, and DCP, is an add-on test to the routine HCC surveillance care with the provisions of abdominal US and AFP every six months.

Japanese investigators have, for several decades, combined AFP with two additional markers, DCP and AFP-L3, for diagnosis and surveillance. DCP, also known as Protein Induced by Vitamin K Absence or Antagonist-II (PIVKA-II) is an immature form of prothrombin [12, 13]. Elevated DCP values (≥ 7.5 ng/ml) are associated with a fivefold increased risk of developing HCC, and on this basis, DCP has received USFDA approval for risk assessment. AFP-L3, a glycoprotein normally produced by the fetal liver, is one of three AFP glycoforms that can be separated based on their lectin binding characteristics, most readily with LCA. An increase in AFP-L3 appears more specific for HCC than total AFP in adults. It is usually presented as a percentage of the total AFP with a reference range of < 10%.

GALAD formally combines these three serum biomarkers together with age and gender to produce an algorithm with better performance than its individual constituents. The GALAD model is of the form: Z = -10.08 + 0.09 × age + 1.67 × sex + 2.34 log (AFP) + 0.04 × AFP-l3 + 1.33 × log (DCP). Where sex = 1 for males, 0 for females.

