### Statistical methods

Bootstrap resampling technique will be used to account for repeated measures to estimate standard errors and confidence intervals. Only MRI nearest to the time of GALAD, US and/or AFP evaluation will be included in the analysis. For time-to-event data, we will use the Cox proportional hazards regression model with covariates tailored to the hypothesis under investigation. For hypotheses involving repeated measurements, events, counts, or other discrete responses, we will use either of two approaches: (1) generalized linear models with generalized estimating equations with robust variance estimation to account for the clustering, or (2) multilevel generalized linear mixed models with random coefficients to account for within-patient clustering as well as other sources of variations like clinic effects.

We will include a random intercept for each hospital site to account for variability by facility. Stratified analyses will be presented for p for interaction < 0.2. Demographic and clinical characteristics will be summarized with proportions and median (minimum–maximum) with no calculation of p-values as this is a non-randomized study. Age at liver disease diagnosis and sex will be accounted for in all analyses. Other confounders of interest include interval follow-up and insurance coverage, whereas age and gender are already controlled in the GALAD (gender, age, etc.) score calculations. All statistical analyses will be performed in SAS 9.4 (or R or another statistical software package with equivalent capabilities).

Baseline descriptions of patients with the standard of care (US and AFP) vs. GALAD score will be compared to each other. Other baseline demographics, biochemical lab results, MRI results, Fibroscan, and abdominal US in the cohort will also be described.

The interim analyses will re-evaluate the performance of the GALAD cut-off score of -0.63 after year 2 of the study. The interim analyses will not be used to assess for study events (i.e., HCC cases), and thus there will be no plan to stop the study if there were no number of events (i.e. HCC cases).

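### Statistical methods contradicts itself on age and sex, so a GALAD regression could refit the locked score; separately, the time-varying Cox model ignores that GALAD brings the MRI forward

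*Protocol article*

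**What the plan says.** The GALAD score section fixes the formula, beginning "Z = -10.08 + 0.09 × age + 1.67 × sex", followed by terms for AFP, AFP-L3 and DCP; "Where sex = 1 for males, 0 for females".

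Statistical methods gives two statements on covariates. The first is "Age at liver disease diagnosis and sex will be accounted for in all analyses". The next sentence names other confounders and adds that "age and gender are already controlled in the GALAD (gender, age, etc.) score calculations".

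The primary evaluation does not rest on a regression coefficient. Outcome measures says "Performance of GALAD score will be determined by using the GALAD score cut-off value of -0.63", and the text after Fig. 2 says "We will compare sensitivity for early HCC detection (primary outcome measures), false-positive results, and resultant diagnostic evaluation". The Cox model is introduced in the abstract as an additional analysis, for "time-to-HCC data as predicted by time-varying biomarker data".

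Under Study schedule and assessments, a liver mass of at least 1 cm, AFP of at least 9 ng/mL or GALAD of at least -0.63 leads to MRI; participants with none of these have MRI annually. Table 1 marks CT or MRI at Visits 1, 3, 5, 7 and 10. With the visit months under Follow-up visits, these fall at 0, 12, 24, 36 and 54 months. Time to event runs to tumour detection on MRI, or to the biopsy date.

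**The concern.** There are two separate problems, both in the regression models.

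**Covariates.** The study sets out to validate an existing score. If sex and an age variable enter beside GALAD, the model no longer holds the score's own weights for them. The result would be reported as a GALAD effect but would belong to a refitted score that no clinic uses. The two sentences point in opposite directions, so two analysts could follow the text and fit different models.

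**Timing.** In the Cox model the exposure helps to decide when the outcome is looked for. Among participants who already have an undetected tumour, a GALAD-positive one is scanned at that visit, while one negative on all triggers waits. The detection hazard is therefore higher at GALAD-positive visits even if GALAD says nothing about HCC, and the error favours GALAD.

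**Working it through.** **A. What adjustment does to the coefficient.** Write Z = c + 0.09·age + 1.67·sex + B, where B is the AFP/AFP-L3/DCP part. A model with Z, sex and current age has linear predictor

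βZ + γ·sex + δ·age = βc + βB + (1.67β + γ)·sex + (0.09β + δ)·age.

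Because γ and δ are free, the sex and age weights are free, and β is the coefficient of B alone. Fitting Z + age + sex and B + age + sex to the same simulated data gave a log-likelihood difference of 0.0.

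The protocol's covariate is age at diagnosis, that is, current age minus disease duration. The age part is then (0.09β + δ)·age − δ·duration. The age weight is still freed, but duration enters too, so the duplication is exact for sex and only approximate for age.

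Logistic fits under assumed distributions (the documents give none) show the possible size:

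| Where the risk lies | Z alone | Z with sex and current age | Z with sex and age at diagnosis |
|---|---|---|---|
| Age and sex only | 0.40 | -0.01 | 0.14 |
| Biomarkers only | 0.35 | 0.80 | 0.60 |
| Exactly as in the locked score | 0.80 | 0.80 | 0.80 |

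In the second row the AUC is 0.653 for locked Z and 0.726 for the model with sex and current age. Adjusted and unadjusted coefficients agree in the third row, where the locked weights are already right; a validation study cannot assume that.

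**B. Hazard ratio for an uninformative marker.** Assume a marker positive at a proportion p of six-monthly visits, independently between visits and of HCC. MRI takes place at the Table 1 visits and at any positive visit. HCC onset is rare, at a constant rate h per half-year. Put q = 1 − p. The scheduled scans leave three gaps of two half-years and one of three.

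- Two-half-year gap. Detection rates summed over visits: positives h[1 + (1 + q)]; negatives h(1 + q).
- Three-half-year gap. Positives h[1 + (1 + q) + (1 + q + q²)]; negatives h(1 + q + q²).
- Total: HR = (9 + 5q + q²) / (4 + 4q + q²).

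At p = 0.10: 14.31 / 8.41 = 1.70. At p = 0.20: 13.64 / 7.84 = 1.74. With strictly annual MRI the ratio is (3 − p)/(2 − p), or 2.9/1.9 = 1.53 at p = 0.10.

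Independence between visits is the extreme case. Simulation with the Table 1 visits and 2% annual onset gives:

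| Chance that a positive stays positive | HR at p = 0.10 | HR at p = 0.20 |
|---|---|---|
| Equal to p (independent) | 1.71 | 1.74 |
| 0.5 | 1.41 | 1.45 |
| 0.7 | 1.24 | 1.26 |
| 0.9 | 1.09 | 1.09 |

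A status that never changes gives about 1.0.

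Ultrasound and AFP triggers also bring scans forward in GALAD-negatives. Let them act independently at a proportion r of visits and put s = (1 − p)(1 − r). Then HR = (9 + 5s + s²) / (4 + 5r + (4 + r)s + s²). At p = 0.10 and r = 0.20, s = 0.72 and the ratio is 13.118 / 8.542 = 1.54. At 90% persistence with other triggers at 10–30% of visits, simulation gives 1.04 to 1.08.

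**C. A tempting remedy.** One could use GALAD from the start of each scheduled-MRI interval. For an uninformative marker that returns 1.00–1.02. But participants still at risk at that point have just had a negative MRI. For a simulated marker that rises only once HCC is present (sensitivity 60–95%, 10% false positives, perfect MRI), the lagged rate ratio is about 1.0, against 24 or more for current status.

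**The case against.** The strongest case against runs as follows.

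- **The locked score is tested.** The primary endpoint uses the fixed cut-off. A reader might infer from the covariate sentence that the trial never evaluates GALAD as used in practice. The documents do not support that, and the point is limited to the Cox, GEE and mixed models. The words on all analyses do literally reach sensitivity and false positives, so the exception should be written down.
- **The second sentence can be read as cancelling the first, and final covariate sets are often left to an analysis plan.** Both are fair. The defect is therefore an unresolved contradiction and not a settled plan to refit the score. It still needs correcting, because the article itself makes both statements.
- **The age covariate differs from the age in the score.** Correct; only sex is duplicated exactly.
- **A hazard ratio of 1.7 is the least plausible case.** Agreed. Sex is constant and age moves slowly, so GALAD status must be correlated within a participant. Positivity, persistence and the rate of other triggers are all assumptions.
- **Nobody is left unscanned.** Test-negatives still have scheduled MRI. A reader might infer missed cancers; the documents support only a shift in detection date.

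**Conclusion.** The point holds for the regression models. Statistical methods gives conflicting rules on age and sex. Following the first frees the sex weight exactly and the age weight approximately, so the GALAD coefficient would mainly describe the biomarker part. The size and direction cannot be known in advance: the illustrative shifts (0.40 to 0.14, or 0.35 to 0.60, with the protocol's age covariate) rest on assumed distributions.

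The timing effect in the additional Cox model is also real and favours GALAD. For an uninformative marker the hazard ratio is about 1.1 at 90% persistence and at most about 1.7 under independence between visits, less once ultrasound and AFP triggers are counted. It vanishes only if status never changes.

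Neither problem undermines the primary sensitivity and false-positive analysis at -0.63.

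**What to change.** 1. Replace the sentence on age and sex. State that sensitivity and false positives at -0.63 are estimated without covariate adjustment, and that regression models of GALAD use the fixed score with site or country only. Label any model that adds age or sex as secondary, as a check of recalibration or of the biomarkers' added value.
2. For time to HCC, treat onset as interval-censored between MRIs. Alternatively, keep the Cox model and report its hazard ratio as affected by GALAD-dependent examination, not as evidence of detection performance.
3. Do not make an analysis with GALAD lagged to the start of the scheduled-MRI interval the main time-to-HCC result. It measures long-range prediction and would miss a marker that rises only when a tumour is present.

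The cost is a change of wording, some extra programming and less precise event timing. No study procedure changes.

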### Authorship

The authorship eligibility guidelines by the International Committee of Medical Journal Editors (https://www.icmje.org/recommendations/browse/roles-and-responsibilities/defining-the-role-of-authors-and-contributors.html) will be followed to determine the authorship contribution.

## Discussion

Assays of AFP, AFP-L3%, and/or DCP have been available for clinical use in a few medical centers in Vietnam over the past five years [14]. Locally, the main indication for the use of the assay is to aid in the risk stratification for HCC in the cases of hepatic nodules with atypical features on cross-sectional imaging for HCC diagnosis, such as without arterial phase hyperenhancement or without delayed phase washout appearance [14]. Other indication, in Vietnam at least, is when AFP has risen upper limits of normal (locally > 9 ng/mL) [14], which often occurs in advanced HCC. There are no consensus national practice guidelines for the use of biomarkers [14]. Similar to Vietnam, GALAD score uptake in Saudi Arabia has not been widely used in clinical practice. Reasons for this include the lack of validated prospective data on GALAD score [6].

Taken together, the combined GALAD score has not been validated and thus utilized systematically for HCC surveillance in Vietnam or Saudi Arabia. Additionally, there is a lack of wide and uniform uptake of GALAD in clinical practice in Vietnam and Saudi Arabia, and there is a need for high-quality research on the use of the GALAD for HCC surveillance. The present work will attempt to fill this evidence gap by evaluating the performance of the GALAD score in early detection of liver cancer. Furthermore, by leveraging the prospective cohort, we will establish a biorepository of longitudinally collected biospecimens from patients with advanced fibrosis or cirrhosis to be used as a reference set for future research in the two countries.

### Confidentiality

All laboratory specimens, evaluation forms, reports, and other records that are part of the study data collection and entry materials will be identified by coded number only to maintain subject confidentiality. All records will be kept in locked file cabinets with access limited to the study investigators. All computer entry and networking programs will identify subjects by participant identification number. Clinical information will not be released without written permission of the subject, except as necessary for monitoring by the IRB or data safety monitoring board. Clinical information may be reviewed during site visits, but the use of personal identifiers will be avoided. Consent procedures and forms as well as the communication, transmission, and storage of participant data will comply with individual site IRB and HIPAA.

## Data Availability

The datasets that will be generated and/or analyzed during the study (to be conducted using this protocol) will be made available appropriately. Corresponding authors may be contacted if someone wants to request the data from this study.

## Abbreviations

AFP: Alpha-fetoprotein
AFP-L3%: Lens culinaris agglutinin bound fraction of AFP
ALT: Alanine aminotransferase
APRI: Aspartate aminotransferase (AST) to platelet ratio index
ARFI: Acoustic radiation force impulse
AST: Aspartate aminotransferase
BCLC: Barcelona Clinic Liver Cancer staging system
CRF: Case report form
DCP: Des-gamma-carboxy-prothrombin
FIB-4: Fibrosis-4 score
GALAD: Gender, Age, AFP-L3%, AFP, and DCP
HBsAg: Hepatitis B surface antigen
HBV: Hepatitis B virus
HCC: Hepatocellular carcinoma
HCV: Hepatitis C virus
HIPAA: Health Insurance Portability and Accountability Act
INR: International normalized ratio
IRB: Institutional review board
LCA: Lens culinaris agglutinin
LiRADS: Liver Imaging Reporting and Data System
MELD: Model for end-stage liver disese
MRI: Magnetic resonance imaging
NASH: Non-alcoholic steatohepatitis
PROBE: Prospective specimen collection and retrospective blinded evaluation
PIVKA-II: Protein induced by vitamin K absence-II
TE: Transient elastography
US: Ultrasound
